**Aim #3: Compare HIV-1 drug resistance patterns in PIC subjects and their source partners.**

*Rationale:* Little is currently known about "transmission fitness", the ability of HIV-1 to infect susceptible hosts. Analyses suggest that drug resistant viruses may be less likely to be transmitted than wild-type viruses [35-38], but data using consensus sequencing show high concordance of mutations in partner pairs [19, 21, 25, 39, 40].

Methods: We will use OLA to compare results of HIV-1 drug resistance testing in PBMCs and plasma from PIC subjects with results of testing in PBMCs, blood and seminal plasma from their confirmed source partners.

Hypothesis: HIV-1 drug resistant variants will be less common and occur at lower levels in the PBMCs and plasma from PIC subjects than in the PBMCs, blood plasma, and genital secretions from their source partners.

Implications: *Transmission probabilities will be quantified from empiric data.* Data from Aim #3 could inform the design of public health interventions to reduce drug resistance by providing data for population models to estimate the proportion of transmitted drug resistance from ARV-experienced and ARV-naïve source partners.

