Compared to consensus sequencing, OLA identified more subjects with transmitted resistance in both plasma (**4a**, p<.0001, by McNemar's exact test) and PBMCs (**4b**, p=.001). There was not a significant difference in the number of subjects with mutations detected by OLA in plasma and PBMCs (**4d,** p=.3).

***Table 5*** *shows the specific mutations that were detected. No subject had the L74V (NRTI) or D30N (PI) mutations. Four subjects had one HIV-1 drug resistance mutation detected by both consensus sequencing and OLA (one with M184V, two with G190A, and one with L90M). The subject with L90M and two other subjects had intermediate genotypes between wild-type and mutant (T215Q and T215D) that were detected by consensus sequencing; screening for T215F and T215Y by OLA yielded indeterminate results. With the use of OLA, the detection of NRTI resistance increased from 4% to 17% of subjects, the detection of NNRTI resistance increased from 2% to 9% of subjects, the detection of PI resistance increased from 1% to 19% of subjects, and the detection of multi-drug resistant HIV-1 increased from 1% to 9% of subjects. Overall, 34% (95% CI 25-44%) of subjects had transmitted HIV-1 drug resistance. These data show our ability to use OLA to identify transmitted low-frequency HIV-1 drug resistance and demonstrate a high prevalence of drug resistance that was not detected by consensus sequencing in our cohort of subjects with primary HIV-1 infection.*

Table 5: Number of subjects with HIV-1 drug resistance mutations detected by OLA in PBMCs, plasma, or both, by mutation

|  | *NRTI* | | | | *NNRTI* | | | *PI* | | | | |
| --- | --- | --- | --- | --- | --- | --- | --- | --- | --- | --- | --- | --- |
|  | *K65R* | *K70R* | *M184V* | *T215F/Y* | *K103N* | *Y181C* | *G190A* | *I50V* | *V82A/S/T* | *I84V* | *N88D* | *L90M* |
| *PBMCs only* | *4* | *2* | *5* | *5* | *2* | *-* | *1* | *1* | *1* | *-* | *4* | *-* |
| *Plasma only* | *2* | *1* | *2* | *3* | *-* | *4* | *-* | *7* | *-* | *2* | *3* | *-* |
| *Both* | *2* | *-* | *-* | *-* | *-* | *-* | *2* | *-* | *1* | *2* | *-* | *1* |

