**5.c Study design and data analysis**

**5.c.1 Aim #1: Determine whether the "level" of detection of HIV-1 drug resistance variants predicts the duration of detection of these variants over time since HIV-1 acquisition.**

Aim #1 will evaluate *the level* of detection of low-frequency HIV-1 drug resistance mutations in PBMCs, blood and seminal plasma from ARV-naïve subjects at baseline and over time. Because we anticipate that no more than 50% of male subjects will provide semen specimens and we will have few female subjects available for study, the study will be powered to compare transmitted HIV-1 drug resistance in PBMCs and blood plasma. We hypothesize that a smaller proportion of subjects will have low-frequency mutations that remain detectable compared to subjects with mutations detected by consensus sequencing at baseline, and a greater proportion of subjects will have mutations that remain detectable in PBMCs compared to blood and seminal plasma.

All subjects selected for study will have baseline testing to detect transmitted HIV-1 drug resistance using both OLA and consensus sequencing. Results of baseline testing will be combined with results from our pilot study to obtain a more precise estimate of the prevalence of transmitted HIV-1 drug resistance in Seattle. Logistic regression analyses will explore subject characteristics potentially associated with transmitted drug resistance including subject age; race/ethnicity; level of education; risk factor for HIV-1 acquisition; year of HIV-1 acquisition; use of methamphetamine, other illicit drugs, or erectile dysfunction medications; number of recent sex partners; and locations for meeting new partners (e.g. bathhouses, internet, etc) [188, 189].

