**5.c.3 Aim #3: Compare HIV-1 drug resistance patterns in PIC subjects and their source partners.**

This cross-sectional study will evaluate the prevalence and patterns of HIV-1 drug resistance in partner-pairs and compare results of HIV-1 drug resistance testing in the PBMCs, blood plasma, and genital secretions (when available) from the confirmed source partner with test results in PBMCs and blood plasma from the recipient partner. We hypothesize that HIV-1 drug resistant variants will have lower "transmission fitness" compared to wild-type variants, and drug resistance will occur less frequently and at lower levels in the PBMCs and plasma from PIC subjects than in the PBMCs, blood plasma, and genital secretions from their confirmed source partners. Because the most common risk for HIV-1 acquisition reported among our cohort is receptive anal intercourse, the ideal comparison would evaluate the results of HIV-1 drug resistance testing in semen specimens from every source partner. However, not all potential source partners collect genital secretions for study. As previous studies have shown that there is moderate concordance between HIV-1 drug resistance testing results in blood and semen [61-63], our proposed comparison using the results of resistance testing in the blood of source partners should have relevance.

For every subject enrolled in the PIC Cohort study, we will attempt to identify and study all source partners through the methods described below in **5.d.2 PIC Partners study** and **5.e Laboratory methods**.If OLA is not performed as part of the other studies previously described in this application, OLA will be performed on the first available PBMC and plasma specimens from PIC enrollees and on the PBMC, blood plasma, and genital secretions from confirmed source partners. We hypothesize that many but not all mutations in the source partner will be identified in the recipient partner and that low-frequency mutations detected in the recipient partner will be present at lower levels compared to their levels in the source partners. Secondary analyses will explore whether the probability of transmission differs between specific HIV-1 drug resistance mutations.

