1Specimens will be collected and stored for future testing. More detailed laboratory studies will only be performed if sequence analysis confirms that transmission occurred from the PIC Partner to the PIC enrollee.

2Collection of semen specimens is recommended but optional.

3An additional 17mL of blood will be collected during a 20 minute visit if the collection of semen specimens is >4 days after Visit #2.

*4Subjects will be offered screening for sexually transmitted infections (STIs) at study entry, including blood for syphilis and HSV serologies, pharyngeal swab for gonorrhea culture, urine for NAAT for gonorrhea and chlamydia, and rectal swab for culture for gonorrhea and chlamydia. These will be transported by courier to the PHSKC laboratory.*

At the initial visit, partners not known to be HIV-positive will be informed of their exposure, asked about symptoms consistent with acute or established HIV-1 infection, and screened for HIV-1 infection. Partners will complete a behavioral questionnaire to ascertain their knowledge of their HIV-1 status and to quantify sexual and needle-sharing exposures to the PIC enrollee. If the partner is found to meet the above criteria for acute or early HIV-1 infection, s/he will be screened for additional studies available through the PIC.

Only HIV-positive partners will complete the additional evaluations and specimen collections listed in **Table 12** as Visit #2 (Entry). This visit may be combined with Visit #1 (Screening) for partners previously known to be HIV-positive. HIV-positive partners will be asked detailed information about their past medical history, including dates of prior HIV-1 testing (to estimate the date of HIV-1 infection), ARV history and previous opportunistic conditions. A physical examination will be performed, including documentation of circumcision status. Blood will be drawn for a CD4+ T-cell count and storage of serum, plasma, and PBMCs. Viral sequencing will be done in the [name] laboratory to confirm the transmission relationship between partners. Collection of genital secretions will be recommended but optional for both male and female source partners. There is no longitudinal follow-up; we anticipate that all partners should complete the evaluations within a few weeks.

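### Aim 3 compares resistance frequency and level in up to three source specimens with two recipient specimens, so the frequency comparison leans toward the hypothesis in pairs whose source gives a genital specimen

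*Protocol*

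**What the plan says.** Section 5.c.3 will "compare results of HIV-1 drug resistance testing in the PBMCs, blood plasma, and genital secretions (when available) from the confirmed source partner". The other side of the comparison has two specimens rather than three: the source results are to be compared "with test results in PBMCs and blood plasma from the recipient partner". The hypothesis uses the same sets. Section 5.c.3 expects that "drug resistance will occur less frequently and at lower levels in the PBMCs and plasma from PIC subjects", and the comparator in section 2, Aim #3, completes the sentence: "than in the PBMCs, blood plasma, and genital secretions from their source partners". The study overview in section 5.a repeats the pairing of two recipient specimens with three source specimens.

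The genital specimen is not universal. Section 5.d.2 states: "Collection of genital secretions will be recommended but optional for both male and female source partners". Section 5.c.3 concedes that "not all potential source partners collect genital secretions for study", calls semen the ideal source specimen given the usual route of exposure, and defends the use of source blood by citing moderate blood-semen concordance.

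Two kinds of Aim 3 output need to be kept apart. The primary objective (5.b, 5.c.3) is the probability that a source mutation is found in the recipient, analysed as a binomial conditional on the mutations found in the source. The frequency hypothesis and the secondary objective on levels are source-recipient comparisons. The only detection adjustment named for Aim 3 is an exploratory one for time between transmission and sampling. No Aim 3 text limits the comparison to compartments tested in both partners.

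**The concern.** Adding a specimen can only add positive calls. If a person counts as positive when any tested compartment is positive, a source tested in three compartments will show more resistance than a recipient tested in two, even when both carry the same variants. That difference has the same sign as the hypothesised loss of transmission fitness. Because the third specimen is optional, the imbalance also differs from pair to pair.

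The pilot shows that one more compartment matters. In Table 4d, OLA was positive in 20 subjects in PBMCs, in 26 in plasma, and in 34 in either. Adding plasma to PBMCs raised the positives by 14/20 = 70%, and adding PBMCs to plasma raised them by 8/26 = 31%. At stake is whether a finding of less resistance in recipients could be read as biology when part of it comes from the number of specimens.

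**Working it through.** **The plan's own Aim 3 figure.** Section 5.c.3 states 82% power with 17 pairs at a transmission probability of 0.80. A simulation of 200,000 replicates gives 82.0% with untruncated Poisson(2) counts and the mean of per-pair proportions. It gives 95.9% if every source has at least one mutation and mutations are pooled, which is the more literal reading. The figure is reproducible, but it takes no account of compartments, so the check below is separate.

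**Inputs from the pilot (section 4.g).**
- Table 4d, subjects: both 12, plasma only 14, PBMCs only 8.
- Table 5 ("Number of subjects with HIV-1 drug resistance mutations detected by OLA in PBMCs, plasma, or both, by mutation"), summed over mutations: PBMCs only 25, plasma only 24, both 8, total 57.

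**Detection per compartment**, estimated as the share of positives in one compartment that are also positive in the other:
- Subject level: plasma 12/20 = 0.600; PBMCs 12/26 = 0.462.
- Mutation level: plasma 8/33 = 0.24; PBMCs 8/32 = 0.25. I use 0.25 for both; the exact fractions move no ratio below by as much as 0.01.

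**Assumptions.** Transmission is complete, both partners carry the same mutations, and detection is constant and independent between compartments. The protocol gives neither the genital detection probability g nor the share a of sources giving a specimen, so both are varied. The nearest guide to a is the Aim #1 expectation for PIC subjects that "no more than 50% of male subjects will provide semen specimens". That is a ceiling, and it is for a different group.

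**Formula.** Let u be the probability that both blood compartments miss a mutation.
- Recipient detection = 1 − u.
- Average source detection = 1 − u + a·u·g.
- Ratio = (1 − u) / (1 − u + a·u·g).

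Subject level: u = 0.400 × 0.538 = 0.215, so recipient detection is 0.785. Mutation level: u = 0.75² = 0.5625, so it is 0.4375.

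| Basis | g | Source detection, a = 0.5 | Ratio, a = 0.5 | Ratio, a = 1 |
|---|---|---|---|---|
| Subject | 0.20 | 0.806 | 0.97 | 0.95 |
| Subject | 0.60 | 0.849 | 0.92 | 0.86 |
| Mutation | 0.125 | 0.473 | 0.93 | 0.86 |
| Mutation | 0.25 | 0.508 | 0.86 | 0.76 |

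With a = 0, or with PBMCs and blood plasma only in both partners, the ratio is 1.00.

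**Primary conditional probability.** Under the same assumptions, the chance that the recipient shows a mutation found in the source is 1 − u, whatever the source's number of specimens. The third compartment has no effect. If detectability q varies by mutation and is shared within the pair, each person's detection is 1 − (1 − q)^k with k compartments. Expected recovery, going from two to three source compartments, then falls as follows:
- q ~ Beta(1, 1): 0.800 to 0.778.
- q ~ Beta(0.5, 0.5): 0.837 to 0.812.
- q ~ Beta(0.5, 1.5): 0.646 to 0.616.

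These are drops of 2 to 3 points under illustrative models.

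**The case against.** The strongest reply is that the plan contains no test of marginal source-recipient frequency. Its one primary objective for Aim 3 conditions on source mutations, and the extra specimen hardly moves that quantity. This stands, and it limits the point to the stated hypothesis and the descriptive and secondary comparisons of frequency and level.

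A second reply is that section 5.c.3 already proposes a comparison using source blood. In context, that sentence explains why blood is acceptable when genital specimens are absent. It does not exclude genital results when they exist, and the same section orders OLA on them and keeps them in the hypothesis. The text is at best ambiguous.

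Third, semen is the relevant specimen for what could be transmitted. That is right, and it argues for a separate genital analysis rather than for counting positives over three specimens against two.

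Fourth, the independence assumption probably overstates the effect. The protocol cites moderate blood-semen concordance, and positive correlation reduces the extra calls. Section 4.e reports seminal HIV-1 RNA 0.7 to 0.8 log10 below blood in untreated men with primary infection, which gives no support for genital detection as good as blood. This stands as a reason to treat the sizes as illustrative.

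A reader might infer something stronger: a 24% deficit in recipients, or false support for the hypothesis in 27% of studies. The documents do not support either. Both need every source to give an optional specimen with detection equal to and independent of blood. The 27% also rests on an exact test of discordant mutations that the plan does not contain; under that borrowed test the rate is about 9% if half of the sources give a specimen. Nor do the documents support the inference that levels must look lower in recipients. That requires taking the highest level across compartments, and no such rule is stated.

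**Conclusion.** The point holds for the Aim #3 hypothesis and for the frequency and level comparisons. The specimen sets are unequal in the text, and in pairs with a source genital specimen the any-compartment frequency comparison leans toward the hypothesis. With half of the sources giving a specimen, the artefact is roughly 3% to 8% on the subject-level basis and 7% to 14% on the mutation-level basis. The direction does not depend on the modelling. The size does: it rests on small pilot counts, assumed independence, and assumed genital detection and availability.

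The point does not undermine the primary conditional estimate, where the effect is 0 to about 3 points. A reader should also not infer that matching compartments would repair that analysis. Its reference value is exactly 1 while recipient detection is imperfect. At the subject-level detection of 0.785 with full transmission, the 95% interval excludes 1 in about 97% of simulated studies (at least one mutation per source, mutations pooled), whether or not genital specimens are used. That is a separate matter.

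**What to change.** In section 5.c.3 and in the Aim #3 hypothesis (section 2), state that resistance frequency and level are compared within compartments tested in both partners: PBMCs with PBMCs and blood plasma with blood plasma. Report source genital secretions in a separate, labelled analysis of what was available to transmit. Where the recipient has baseline semen OLA, which section 5.a and Figure 5 already plan for PIC subjects, add a semen-to-semen comparison in those pairs. Leave the primary conditional estimand in place.

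The cost is analysis wording only, with no new specimens or assays. The downside is that mutations found only in source genital secretions leave the matched frequency and level comparison and appear only in the separate analysis.

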Analysis for the primary objective will be calculated as a binomial probability of the number of mutations transmitted from each source partner to the recipient partner, conditional on the number of mutations in the source partner. This accounts for the fact that source partners will undoubtedly have different numbers of HIV-1 drug resistance mutations. For the purpose of sample size calculations, we assume that the number of mutations in the source partners follows a Poisson distribution with the expected number of mutations being two. Power calculations are based on simulations, repeated 1000 times. Each simulation estimates the binomial probability of transmitting a mutation conditional on the number of mutations in the source partners, and calculates the associated 95% confidence intervals based on normal approximation for the estimated probability. The type II error is calculated as the number of simulation replicates where the 95% confidence interval contains the value of 1, when the simulated transmission probability is less than 1.

Using the simulation analyses described above, we will have 82% power to detect a transmission probability of all source partner mutations of 80% or less if we have 17 confirmed partner-pairs in which the source partner has at least one HIV-1 drug resistance mutation. *Overall, the subset of recipient partners who had resistance identified by OLA (4/12=33%) was similar to the population studied in the pilot project. Of the 18 confirmed partner pairs without complete OLA testing, we would expect 6 to 18 source partners to have HIV-1 drug resistance. Based on our prior experience with confirming putative source partners, we would expect that the relationship of 14 of the remaining 17 partner-pairs would be confirmed, and 5 to 17 of these source partners would have HIV-1 drug resistance. We would therefore need to enroll at most 21 (and likely fewer) new putative source partners in order to have at least 6 additional confirmed source partners with HIV-1 drug resistance.*

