To further explore which specific mutations are more likely to be transmitted and result in subsequent HIV-1 infection, we will conduct a logistic regression analysis with generalized estimating equations to account for correlation of the presence of different mutations within the same source partner. In this analysis, each individual mutation will be evaluated, with the outcome in the regression model; transmitted to partner Yes/No. Indicator covariates will be used to identify specific mutations. To account for the potential loss of detection of mutants over time, an exploratory analysis will adjust for the estimated time between the transmission event and the dates samples are obtained from the transmission pair for HIV-1 drug resistance testing.

We will also use the semi-quantitative nature of OLA to categorize HIV-1 drug resistance mutations as comprising <5%, 5-10%, 10-30%, 30-50%, and 50-100% of the viral quasi-species. We will compare the level of specific HIV-1 drug resistance mutations in the source and recipient partners to identify, for example, whether a mutation exists as 5-10% of the population in the source partner but 10-50% in the recipient. Analyses will control for HIV-1 RNA levels at the time of HIV-1 transmission.

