**5.f.4 Power**

As previously mentioned, this study has limited power for the analysis comparing the time to virologic failure among subjects with and without transmitted HIV-1 drug resistance who initiate ARV therapy. We will instead perform an analysis comparing the time to virologic suppression, which has been used as a surrogate outcome by other seminal studies that evaluated the impact of transmitted drug resistance on the response to ARV treatment [52, 53, 56, 190]. In addition, the time to virologic suppression and other markers of early treatment response have been associated with longer-term treatment outcomes [191-193]. If our results suggest that transmitted low-frequency HIV-1 drug resistance has an adverse impact on response to ARV therapy, a randomized clinical trial will be designed to definitively answer these questions.

These studies will also not have sufficient power to identify specific mutations that may be particularly clinically relevant (e.g. K103N) because of the infrequent transmission of any one particular HIV-1 drug resistance mutation and the frequent co-transmission of mutations. Similarly, we will not be able to determine if there are differences in the rate of loss of detection or compare rates of transmission between specific mutations.

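### The Aim 3 primary interval and its 82% power treat mutations from one source partner as independent, although the plan itself describes frequent co-transmission

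*Protocol*

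**What the plan says.** Quantifying the probability of transmission is the only primary objective of Aim 3 (section 5.b). Section 5.c.3 fixes the method: "Analysis for the primary objective will be calculated as a binomial probability of the number of mutations transmitted from each source partner", conditional on the number of mutations in the source. The reason given for conditioning is: "This accounts for the fact that source partners will undoubtedly have different numbers of HIV-1 drug resistance mutations".

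For sample size, "we assume that the number of mutations in the source partners follows a Poisson distribution with the expected number of mutations being two". The section continues: "Power calculations are based on simulations, repeated 1000 times". Each replicate "calculates the associated 95% confidence intervals based on normal approximation for the estimated probability", and a replicate counts as a miss when that interval contains 1. The result is that "we will have 82% power to detect a transmission probability of all source partner mutations of 80% or less", given 17 confirmed pairs in which the source has at least one mutation.

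Two other places bear on independence. Later in section 5.c.3, the exploratory model for specific mutations, whose outcome is transmitted yes/no, uses GEE "to account for correlation of the presence of different mutations within the same source partner". Section 5.f.4 explains the limited power for specific mutations partly by "the frequent co-transmission of mutations".

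**The concern.** A partner-pair contributes one transmission event. If mutations tend to pass, or fail to pass, together, several mutations from one source carry less information than the same number from different sources. Conditioning on the source's count sets the denominator for each pair. It does nothing about dependence among the outcomes within the pair. The plan therefore allows for clustering in an exploratory model and not in the primary estimate of the same aim.

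Two things are at stake. The interval around the transmission probability would be too narrow, and section 5.h.4 sends that probability into mathematical models of transmitted resistance. The 82% power supports the 17-pair target, and through it the figure of at most 21 new putative source partners, yet it is calculated as if mutations were independent.

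**Working it through.** **Inputs from section 5.c.3:** 17 pairs; mutations per source Poisson with mean 2; at least one mutation per source; true probability 0.8; two-sided 95% normal-approximation interval; success when the upper limit is below 1. **Assumed:** the within-pair ICC, which the protocol does not give.

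**Step 1. Number of mutations.** Mean two gives 17 × 2 = 34 mutations. A Poisson with mean 2 has no mutation in e⁻² = 13.5% of sources, so mean two and at least one mutation do not fit together without adjustment. Dropping the zeros from a Poisson(2) raises the mean to 2/(1 − e⁻²) = 2.31, or 39.3 mutations in all. Keeping at least one and a mean of two needs a lower underlying rate and again gives 34.

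**Step 2. Reproduce the 82%.** The section does not say how the standard error is formed. Power by simulation, with independent binomial outcomes pooled over pairs:

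| Form of interval | Zeros allowed, mean 2 | At least one, mean 2 | Poisson(2) without zeros |
|---|---|---|---|
| SE fixed at p = 0.8 | 0.82 | 0.82 | 0.88 |
| Wald with continuity correction | 0.81 | 0.82 | 0.90 |
| Plain Wald | 0.91 | 0.92 | 0.96 |

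A hand check with exactly 34 mutations:

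- SE at 0.8: √(0.16/34) = 0.0686, and 1.96 × 0.0686 = 0.134. Success needs at most 29 of 34 transmitted (29/34 + 0.134 = 0.987; 30/34 + 0.134 = 1.017). The binomial probability is 0.838.
- Plain Wald: 30 of 34 gives an upper limit of 0.882 + 1.96 × 0.0553 = 0.991, and 31 of 34 gives 0.912 + 1.96 × 0.0486 = 1.007. Success is at most 30, with probability 0.930.

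So 82% is attainable with independent outcomes and about 34 mutations. It is not what a plain Wald interval gives.

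**Step 3. Effect of correlation on the interval.** The design effect is 1 + (Σm²/Σm − 1) × ICC. For Poisson(2), E(m²)/E(m) = (2 + 4)/2 = 3, so it is about 1 + 2 × ICC. The table uses beta-binomial outcomes, p = 0.8, 17 pairs, zeros allowed.

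| ICC (assumed) | Design effect | Required width ÷ stated width | Coverage of unadjusted 95% Wald interval |
|---|---|---|---|
| 0 | 1.00 | 1.00 | 92% |
| 0.1 | 1.19 | 1.09 | 90% |
| 0.3 | 1.58 | 1.26 | 85% |
| 0.5 | 1.97 | 1.40 | 79% |
| 1 (all-or-none) | 2.94 | 1.71 | 69% |

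Poisson(2) counts without zeros give nearly the same coverage: 93%, 90%, 85%, 80% and 70%. The 92% at ICC 0 is the normal approximation's own shortfall at this size. At p = 0.9 and ICC 0, coverage is about 90%.

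**Step 4. Effect on power, with the standard error multiplied by the square root of the design effect.**

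| ICC | Variants that reproduce 82% | Plain Wald variants |
|---|---|---|
| 0 | 81–82% | 91–96% |
| 0.1 | 74–79% | 85–91% |
| 0.3 | 58–65% | 68–78% |
| 0.5 | 44–56% | 54–64% |

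**The case against.** **The method may already work at pair level.** Averaging per-pair proportions, with zero-mutation sources allowed, also gives 0.82. That interval's coverage hardly depends on the ICC: 89.0%, 89.3%, 89.3% and 87.8% at ICC 0, 0.3, 0.5 and 1. If that were the plan, the interval point would largely fall away. But the text describes a binomial probability of transmitting a mutation, and the simulated outcomes would still be independent. The objection shows that the method needs stating.

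**A reader might infer that the 82% is inconsistent with the stated method, or arises only by letting sources have zero mutations.** The documents do not support this. Normal approximation does not fix the form of the standard error, and an SE at p = 0.8 gives 0.82 with every source having at least one mutation and a mean of two.

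**A reader might infer that true power is some low figure, or that more pairs are required.** Neither follows. A symmetric cluster-robust t interval gives 73%, 59% and 28% at ICC 0.3, 0.5 and 1 (Poisson(2) without zeros), but that is one interval among several, and it covers only about 91% at ICC 0.3. The reference value is exactly 1, and an interval suited to that boundary can exclude 1 after a single failure. Even all-or-none, at least one failure in 17 pairs has probability 1 − 0.8¹⁷ = 97.7%. Section 5.c.3 also expects 6–18 plus 5–17, that is 11–35, resistant source partners before new enrolment, so 17 is not a ceiling.

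**The supporting quotes are limited.** The GEE sentence concerns presence of mutations in the source, and the co-transmission remark is made about mutation-specific power. Neither gives a degree of correlation. This stands for the size of the effect. It does not remove the direction, since co-transmission is a statement about outcomes moving together.

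**Variance estimators are often left to an SAP.** Here, however, the protocol itself fixes the model, the interval and the simulation.

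**Conclusion.** The concern holds for the primary estimate as written. Under the pooled-binomial reading, with 17 pairs and p = 0.8, the nominal 95% interval falls short even at independence and loses further coverage as mutations become co-transmitted, to about 80% at an ICC of 0.5. These sizes rest on an ICC range that I have assumed and on a beta-binomial model.

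The 82% is reproducible, but under independence and with an interval form that the text does not name. There is no inflated error against the null value: if the probability is 1, every mutation is transmitted and the interval cannot exclude 1. The damage is to the precision claimed for the estimate and to the basis of the power figure. It is worth correcting before analysis, but it does not invalidate the aim or show that 17 pairs are too few.

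**What to change.** 1. Give the primary estimate a pair-level variance: a beta-binomial model, an intercept-only GEE with small-sample correction, or a bootstrap that resamples pairs. Choose an interval whose coverage near 1 has been checked by simulation at this number of pairs.
2. Rerun the power simulation with every source having at least one mutation, over a stated ICC range such as 0 to 0.5. Name the interval form and the count distribution.
3. Replace the single 82% with the resulting range. This correction alone does not call for more pairs.

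The cost is some wording and a rerun simulation, with no new data or procedures. The downside is a wider interval and possibly a less favourable stated power.
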